### Objectives

This paper describes the protocol of a pragmatic randomized controlled trial (RCT), PAC-WOMAN, targeting Portuguese post-menopausal women diagnosed with hormone-receptor-positive breast cancer, currently on Aromatase Inhibitors. This project primary aims are:a) To develop and test the long-term (16-month) effectiveness and cost-effectiveness of two 4-month group-based interventions, compared to a control waiting list, on promoting sustained changes in PA, sedentary behavior, QoL, and healthcare services’ use (primary outcomes)b) To compare the effects of both interventions (i.e., brief PA counseling vs. structured exercise) on long-term changes in our primary outcomes, as well as their cost-effectivenessc) Evaluate pretreatment moderators of 4-month and 16-month changes in PA, sedentary behavior, and QoLd) Identify critical motivational (theoretical) mechanisms of change in PA, sedentary behavior, and QoL, and explore their mediating role.

As secondary aims, we will study the impact of both interventions on AI therapy continuation, adverse events of treatment, disease-free survival, body composition, sleep quality, physical parameters (e.g., muscular strength), and psychosocial factors (e.g., body image). Furthermore, process evaluation will also be conducted seeking to analyze implementation facilitators and barriers.

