#### Randomization and blinding

After signing the informed consent and completing the baseline assessments, participants are randomly allocated to one of the three arms. Allocation is being made according to an automated computer-generated randomization scheme performed by a member of the research team not directly involved with participants. Adjustments in the allocation ratios might be made if recruitment takes longer than expected and interventions are required to start for timely reasons. Group assignment is only communicated to participants after all baseline testing is finished.

Participants and research team staff are unaware of group allocation at the time of recruitment and baseline assessments because randomization is only performed after participants have completed baseline assessments. This study will involve behavior change interventions, preventing any concealment of group allocation after randomization from either participants or intervention counsellors. Nonetheless, participants will be blinded to the study rationale. Also, to minimize bias, physical activity and sedentary behavior (primary outcomes) are objectively assessed using accelerometers and psychometric data are collected by self-report and introduced in the Qualtrics platform in its raw state. All outcome data will be kept blinded until the final data entry for the entire study is completed.

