#### Strategies to improve adherence to interventions and follow-up assessments

One of the major risks in this study is the low compliance of patients to the interventions and assessments. Although most cancer survivors manifest interest in participating in physical activity [15], their lifestyle and implemented routines may interfere with their participation. In addition, a severe decline in physical function is expected to occur during AI therapy, which could potentially lead to increased dropout rates. Nonetheless, the research team includes medical oncologists, physiatrists, and qualified exercise professionals that will assure a close proximity with participants throughout the course of the intervention, assess their experiences and opinions about the program and ways of improving it, and provide a rationale for all the activities involved in the intervention, making sure they continue committed to the trial’s protocol. Moreover, a qualitative analysis (through focus groups) will be applied to enhance the understanding of the patients’ perspectives about: the impacts of the intervention in their daily life; benefits and disadvantages of participation; functional aspects (e.g., dose, procedures, structure) of the intervention; and suggestions of improvement. To increase adherence to follow-up assessments, a session on healthy nutrition for cancer survivors will be offered at this point, as this is a topic that gets a lot of interest among women. Also, at each assessment timepoint, a treat will be offered to participants to stimulate their adherence to the evaluations (e.g., using the gym pool for the day of assessments; a week voucher to try out different gyms), scheduled at a time of their convenience. Participants will also receive an early reminder of the approaching assessment point, and then gentle reminders confirming the date, time, and location of their upcoming visit on the day before.

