#### Assessments

Participants will be assessed at four time points: baseline (T_0_), 4 months (intervention’s end; T_1_), and 10 and 16 months (T_2-_T_3_; during follow-up). A schematic description of all the measurements by timepoint is presented in Table 2. Assessments will take place in standardized conditions, at the exercise setting, in a calm comfortable environment, in small groups, with a group of study technicians attending every assessment period. At each assessment point, the research staff provides participants with an accelerometer, which they are required to wear for a week, and schedules an evaluation visit to the exercise setting, where participants complete the full battery of assessments, described below, and according to the assessment plan for that timepoint. An individual report with the assessment results will be provided to each participant at the end of each assessment period is complete. Participants will be contacted close to each assessment point to determine any changes in their contact or personal information that may have occurred, especially in the fulfillment of the eligibility criteria.

**Table 2 Tab2:** Measurements’ timeline

	**Intervention**		**Follow-up**	
	**T0 Baseline**	**T1 4 months**	**T2 10 months**	**T3 16 months**

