**Secondary outcomes – Physical Measures**				
Body composition	X	X	X	X
Cardiorespiratory fitness	X	X	X	X
Muscular strength	X	X	X	X
Upper limbs flexibility	X	X	X	X
Physical function	X	X	X	X
Adverse events	X	X	X	X

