Physical Function. The Sit to Stand, Timed Up and Go and Stand on one-foot tests are employed to assess physical function. The Sit to Stand Test consists of standing and seating in a chair as many times as possible with arms crossed over the chest in 30 s [73]. The Time Up and Go Test is used to assess mobility by measuring the time a person takes to rise from a chair, walk 2.44 m, turn around, walk back to the chair, and sit down [74]. For the Stand on one foot test [75], participants are instructed to stand on one foot with their eyes open (both sides are tested) for a maximum of 20 s and have their time recorded.

Adverse events of anticancer treatment. A simplified version of the Common Terminology Criteria for Adverse Events (CTCAE v.5), using its broader categories (i.e., cardiac disorders, respiratory disorders, nervous system disorders, infections, skin tissue disorders, musculoskeletal and connective tissue disorders, and immune system disorders) is used at each timepoint to assess the occurrence of any adverse events in the previous 3 months.

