#### Statistical methods

Factorial Anovas with repeated measures, adjusting for potential covariates (e.g., primary treatment, length of AI therapy), will be conducted for primary and secondary outcomes. The analysis will be intent-to-treat to include compliance effects in the overall assessment. Last Observation Carried Forward will be used to impute missing values. A per-protocol analysis will also be conducted without participants who do not attend at least 80% of the sessions. Normality plots and Kolmogorov–Smirnov tests will be used to test normality of outcome variables. If substantial departure from normality is found, square root log transformations will be computed. If normality is still not satisfied, non-parametric tests (e.g., Kruskal–Wallis) will be employed. As the experimental design is factorial, multiple comparison adjustments will not be appropriate.

Mediators of change, i.e., mechanisms by which participants change their lifestyle behaviors and QoL (vs. controls), will be explored using structural equation modeling (AMOS 18.0) and multiple mediation analysis (PROCESS macro v. 3.3 for SPSS). Putative candidates will include motivational (e.g., autonomous motivations) and self‐regulatory (e.g., action planning) variables. Mediation is said to occur when the causal effect of an independent variable (X) on a dependent variable (Y) is partially or fully explained by a mediator (M) [93]. Indirect effects will be tested using Preacher and Hayes’ procedures [94]. Bootstrapping with 5000 samples and 95% CI estimates for indirect effects will be calculated and assumed significant (α = 0.05) if the CI does not encompass zero [95, 96]. The ratio of the indirect effects to the total effects (P_*M*_) will be calculated to express the strength of the mediation effects [95]. Moderators, i.e., baseline characteristics that have an interactive effect with the intervention on the outcome(s), will be assessed to better understand individual differences in intervention effects [97, 98]. Moderation effects on primary outcomes will be conducted at intervention or follow-up’s end.

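### As written, the last-observation-carried-forward rule would fill a missed 3-month adverse-event window with an answer about a different, non-overlapping window

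*Protocol article*

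**What the plan says.** The Objectives section of the protocol article makes adverse events part of the secondary aims: "we will study the impact of both interventions on AI therapy continuation, adverse events of treatment". Table 2 lists them among the secondary physical measures at all four visits: "Adverse events X X X X". The paragraph on adverse events of anticancer treatment describes a simplified CTCAE questionnaire that "is used at each timepoint to assess the occurrence of any adverse events in the previous 3 months". The Assessments section sets the visits at baseline (T0) and at 4, 10 and 16 months (T1 to T3). Under Randomization and blinding, "randomization is only performed after participants have completed baseline assessments".

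Statistical methods then gives one analysis and one missing-data rule: "Factorial Anovas with repeated measures, adjusting for potential covariates (e.g., primary treatment, length of AI therapy), will be conducted for primary and secondary outcomes", and "Last Observation Carried Forward will be used to impute missing values". Neither sentence names an exception. If normality fails after transformation, non-parametric tests replace the ANOVA, but nothing says that the missing-data rule changes with them.

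Other safety data are collected separately. Exercise-related effects are registered in sessions (Interventions). Participants also self-report at sessions and are asked to contact the clinical team between visits if they have difficulties (Adverse event reporting and harms).

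**The concern.** Carrying a score forward assumes that a state persists. The adverse-event item does not measure a state. It asks whether something happened in a dated 3-month window. If the windows do not overlap, the carried answer is an observation of a different period, entered as if the missing period had been observed. For a woman with no visit after baseline, the value entered at T1, T2 and T3 was given before she was allocated to anything, so it can carry no intervention effect.

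At stake is the comparison of this outcome between arms. The visit questionnaire is the scheduled measure common to all three arms. Session capture cannot replace it, because the waiting-list arm has no sessions. Moving to a non-parametric test would not help, because the test would run on the same filled values.

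**Working it through.** **1. Recall windows.** Inputs: visits at 0, 4, 10 and 16 months (Assessments) and 3-month recall (Adverse events of anticancer treatment). Window = [t − 3, t] in months from baseline.

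| Visit | Window | Gap from previous window |
|---|---|---|
| T0 | −3 to 0 | – |
| T1 | 1 to 4 | 1 month |
| T2 | 7 to 10 | 3 months |
| T3 | 13 to 16 | 3 months |

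All six pairwise overlaps are 0 months, and the T0 and T3 windows are 13 months apart. T1 would have to fall more than 1 month early to overlap the T0 window.

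**2. How many values could be filled.** The plan's own total reproduces: 98 × 1.25 = 122.5, stated as 122 (Participants). It is not in dispute and serves only to set the scale. Assuming equal allocation, 122/3 = 40.7, taken as 41 per arm. With the planned 25% dropout, 0.25 × 41 = 10.25, about 10 per arm. The timing of loss is not given. If loss is even over 16 months:

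- T1: 10.25 × 4/16 = 2.6, about 3 of 41 (7%)
- T2: 10.25 × 10/16 = 6.4, about 6 of 41 (15%)
- T3: about 10 of 41 (24%)

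If half of the loss comes before T1, about 5 of 41 (12%) are filled there. If all of it does, 10 of 41 (24%), which is an extreme case.

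**3. Error in one arm.** Error = share filled × (carried rate − true rate among the women lost). The article gives no event rates. For an assumed 30-point gap at T1:

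- 3/41 × 30 = 2.2 points
- 5/41 × 30 = 3.7 points
- 10/41 × 30 = 7.3 points

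The sign depends on which rate is higher.

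**4. Difference between arms, equal loss.** If baseline rates are equal and loss is unrelated to events, the filled values are the same in both arms on average, so the difference is multiplied by (1 − share). For an assumed true difference of 15 points:

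- 3 lost per arm: 15 × 38/41 = 13.9
- 5 lost per arm: 15 × 36/41 = 13.2
- 10 lost per arm: 15 × 31/41 = 11.3

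**5. Difference between arms, unequal loss.** Assume 10 lost in an intervention arm, 5 in control, and true rates of 35% and 20%. Then the difference = [(31 × 35 + 10 × b) − (36 × 20 + 5 × b)]/41, where b is the T0 rate in per cent. The true 15 points becomes 10.1 at b = 10, 15.0 at b = 50 and 18.7 at b = 80. If both arms are truly 20%, the spurious difference is (5 × b − 5 × 20)/41 = −1.2, 3.7 or 7.3 points. The last value needs a 60-point gap between the T0 rate and the later rate.

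**6. Precision.** Assume about 29% occurrence. Exact (Clopper-Pearson) 95% intervals:

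- 9/31 observed: 14.2% to 48.0%, width 33.8 points
- 12/41 with 10 values filled: 16.1% to 45.5%, width 29.4 points

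The filled analysis looks 4.4 points narrower without any added observation.

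**The case against.** The strongest reply concerns reach. The analysis paragraph reads as if written for continuous scores (ANOVA, normality checks, transformations) and never mentions adverse events. A reader might infer that the trial has definitely decided to carry a checklist of event categories forward, and the text does not go that far. It does apply its methods to secondary outcomes and it lists adverse events among them. The rule therefore covers them as written, and objecting to a stated rule is not asking for a missing detail.

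A second reply is that this is only the usual complaint about carrying forward. In part that is right. Other measures at these visits also use short recall, such as the Activity Choice Index over the last month, and every T0 value precedes randomisation. What is particular here is that the outcome is occurrence within a stated window, not a level that might plausibly persist.

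A third reply is that T0 is not treatment-free, and this stands. Women must have been on AI therapy for at least 1 month, and the measure concerns events of anticancer treatment. The T0 answer is pre-intervention but not pre-AI.

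Finally, a reader might take the adherence section's statement that "a severe decline in physical function is expected to occur during AI therapy, which could potentially lead to increased dropout rates" as evidence that the women lost have more events, so that the rule hides harm. That passage concerns physical function and dropout and says nothing about event occurrence, so it does not fix the direction of bias.

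**Conclusion.** The point holds for the rule as written. Carrying forward would enter answers about one 3-month period as observations of another and, for women lost before T1, would enter pre-intervention answers as outcomes. The non-overlap follows from the article's own schedule, provided visits occur near their nominal times. The overstated precision follows from counting unobserved windows as observed.

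The size is much less certain. Event rates, timing of loss and differences in loss between arms are all assumed. With even loss the T1 effect is modest: 3 of 41 values filled per arm, and 15 points reduced to 13.9 under the neutral assumptions. The larger figures need extreme inputs, either all loss before T1 or a very wide gap between T0 and later rates. It would be tempting to conclude that the interventions will look safer, or less safe, than they are. The article supports neither.

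One secondary outcome is affected. No primary result or sample-size figure changes, and events registered in sessions or reported between visits are untouched by the rule.

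**What to change.** In Statistical methods, state that adverse-event occurrence is exempt from last observation carried forward and from the repeated-measures ANOVA default. At each post-randomisation visit, report by randomised arm the number and proportion of women with at least one event among those assessed, with exact 95% confidence intervals and the number missing. Use T0 as background only. Report session-registered and between-visit events in separate tables, noting that session capture exists only in the two intervention arms and gives no comparison with control.

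The cost is a short change of text and a few tables from data already planned. There are two downsides. This outcome would have no covariate-adjusted p-value, and proportions among assessed women may still be biased if the women lost differ.

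One optional addition could reduce that second problem. The Assessments section already plans a contact near each visit: "Participants will be contacted close to each assessment point to determine any changes in their contact or personal information that may have occurred". The adverse-event questions could be asked then of women who will not attend but have not withdrawn consent. That would be additional data collection and is not part of the correction.

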#### Interventions

The brief PA counseling (PAC) program will comprise 8 sessions (120 min each), every fifteen days, addressing the following themes: reasons to change, an introduction to the PAC-WOMAN program and principles, types of physical activity and their benefits, strategies on how to become more active and less sedentary, how to safely practice exercise at home, the importance of social support for doing more physical activity, barriers and facilitators for becoming more active, development of coping plans and strategies to overcome those barriers, establishing SMART goals, self-monitoring, medical aspects related to symptom management in breast cancer survivors, body image and self-acceptance, sharing experiences with role models, and re-evaluating action plans.

To increase the potential for long-term behavior change, it is important to target theoretically proposed mechanisms of change and incorporate evidence-based behavior change strategies. Self-Determination Theory (see Rationale for the PAC-WOMAN trial), and several evidence-based behavior change techniques, will be used throughout the intervention. The goal will be to empower participants to develop self-regulation resources, fueled by autonomous motivation to integrate physical activity into daily lives, even in the face of adversity, and thus sustain changes in physical lifestyle. The basic psychological needs of autonomy, competence, and relatedness [28] will be supported in all sessions and intervention materials. More specific SDT-based behavior change strategies will include the provision of choice, meaningful rationale, connection between participants’ health behavior and deep inner values, goal setting, action planning, self-monitoring, coping planning, weighing pros and cons of change in the context of held values and life priorities. Group-based sessions will allow the exchange of experiences, feelings, difficulties, and effective solutions to overcome them, in a respectful, non-judgmental, and supportive environment. The portfolio of strategies, and intervention motivational climate, is in accordance with systematic reviews in this regard [41]. Exercise professionals, previously trained in brief counseling skills for health behavior change and its implementation, will deliver the sessions.

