A participants’ manual was developed, including a toolbox supporting each session. An activity tracker will be provided to all participants to facilitate self-monitoring. An Exercise Booklet was also created, including different exercises that can be performed at home, accompanied by QR codes with complementary instructive videos. An invested role model (a women previously diagnosed with breast cancer) will illustrate the exercises in the booklet during one of the sessions to show the easiness of their completion. Participants will be prompt to use the booklet as they see fit, during their daily lives, in an integrated fashion (passible to be integrated in the long term) and at a self-selected pace.

The structured exercise program was designed based on the most recent guidelines for exercise prescription and safe practice in cancer populations [12, 19, 59]. A group-based supervised program comprising 32 sessions (over 4 months), lasting 90 min each, and taking place twice a week, was developed. The program combines mobility, aerobic, and strength exercises, respecting a periodization model of four mesocycles of 8 sessions, with progressive intensity and complexity, following the periodization model for each exercise component. Once every 15 days, a thematic group class will be offered to participants, so that they can explore different physical activities and enhance their exercise experience.

Each session will be organized into four components: (i) warm-up—a 10 to 30-min combination of articular mobility exercises and body weight activities; (ii) muscular strength—30 to 45 min, 6–7 large muscle group exercises with an intensity of 60–80% of one maximal repetition (10–15 repetitions, 2–3 sets); (iii) aerobic training—20 to 30 min of a cardiorespiratory workout modality chosen according to participant’s preferences (treadmill, elliptic, bike and row machine) with an intensity of 40–60% of reserve heart rate; (iv) cool-down (5 min). Group sessions will be provided in a person-centered, positive interpersonal environment, by qualified exercise professionals.

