An individualized target zone intensity will be previously determined for each participant, based on a preliminary physical evaluation, and monitored during exercise sessions using perceived exertion scales [60] and heart rate monitors (*Polar Club software*). During the sessions, participants’ potential exercise-related adverse effects will be monitored and registered, as well as individual attendance and intensity zone compliance. If participants present any limitations during the session, the exercise prescription will be adapted to respect their individual needs.

Patients allocated to the control group (i.e., waiting list) are asked to continue their daily routines, receiving their standard medical care. No additional instructions will be given to the control group. At the end of the study, the control group will be offered the structured exercise program for 4 months. This type of control group was chosen to allow us to clearly establish whether the tested interventions are effective and superior to no intervention at all.

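### The supplementary per-protocol analysis filters only the two active arms on attendance, so its control contrasts compare self-selected attenders with an unselected arm

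*Protocol article*

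**What the plan says.** Under Statistical methods, the main analysis follows randomisation: "The analysis will be intent-to-treat to include compliance effects in the overall assessment". A second analysis is then added: "A per-protocol analysis will also be conducted without participants who do not attend at least 80% of the sessions". The sentence names no arm.

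The Interventions section gives the number of sessions in each arm:
- PAC: "The brief PA counseling (PAC) program will comprise 8 sessions (120 min each), every fifteen days".
- StEx: "A group-based supervised program comprising 32 sessions (over 4 months), lasting 90 min each, and taking place twice a week, was developed".
- Control: "Patients allocated to the control group (i.e., waiting list) are asked to continue their daily routines, receiving their standard medical care". A programme comes only later: "At the end of the study, the control group will be offered the structured exercise program for 4 months".

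The comparison with the waiting list is the first primary aim under Objectives, where the two interventions are "compared to a control waiting list, on promoting sustained changes in PA, sedentary behavior, QoL, and healthcare services’ use (primary outcomes"). The Process Evaluation section says that facilitators record attendance in a weekly logbook.

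**The concern.** A per-protocol set is open to bias when the women removed from one arm have no counterparts removed from the other. Here that follows from the design. Attendance exists only in PAC and StEx, so poor attenders leave those arms, while the control women who would have attended poorly stay in.

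The article itself gives reasons to expect attendance to be related to outcome. Background and rationale lists lack of motivation, fatigue and pain among the barriers to exercise. The section on strategies to improve adherence treats low compliance as a major risk and links expected functional decline to dropout. Each of these plausibly predicts physical activity and quality of life, both primary outcomes, in women given no programme.

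Because low compliance is named as a major risk, readers are likely to take the per-protocol result as the effect of receiving the intended dose. If selection accounts for part of it, that effect is overstated.

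**Working it through.** The plan gives no figure for this analysis, so there is none to reproduce. The check has three steps.

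**1. What the rule means in each arm.**
- PAC: 0.80 × 8 = 6.4, so 7 sessions; 7/8 = 87.5%, one absence allowed.
- StEx: 0.80 × 32 = 25.6, so 26 sessions; 26/32 = 81.25%, six absences allowed.
- Control: no sessions, so there is nothing to filter on.

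**2. Difference produced by selection alone.** Suppose there is no true effect. Let attendance propensity and untreated outcome be jointly normal with correlation r, and keep the top fraction q of attenders in an active arm and all controls. The expected difference in outcome SD units is r × φ(z)/q, where z is the normal quantile at 1 − q. The multiplier φ(z)/q is 0.798, 0.644, 0.497 and 0.350 for q = 0.5, 0.6, 0.7 and 0.8. Neither r nor q is in the document; both ranges are assumptions.

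| Fraction kept | r = 0.1 | r = 0.2 | r = 0.3 | r = 0.4 |
|---|---|---|---|---|
| 50% | 0.08 | 0.16 | 0.24 | 0.32 |
| 60% | 0.06 | 0.13 | 0.19 | 0.26 |
| 70% | 0.05 | 0.10 | 0.15 | 0.20 |
| 80% | 0.04 | 0.07 | 0.11 | 0.14 |

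A simulation of an unadjusted two-sided 5% t-test with no true effect used 41 women per arm before exclusion (122/3, assuming equal allocation) and 5,000 runs per setting. It rejected in 6.7% to 8.5% of runs at r = 0.2, and in 9.3% to 14.0% at r = 0.3, as the fraction kept fell from 70% to 50%.

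These figures relate attendance to the level of the outcome. Physical activity and quality of life are also measured at baseline, and the planned analysis is a repeated-measures ANOVA. In a comparison of change, stable differences between women largely cancel, and what then matters is the correlation of attendance with untreated change. The table is therefore a range before adjustment and does not predict the bias in the planned model.

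**3. Whether rounding makes the rule stricter in one active arm.** If every woman attends each session independently with the same probability p, the share meeting the rule is a binomial tail probability.

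| p | PAC, at least 7 of 8 | StEx, at least 26 of 32 |
|---|---|---|
| 0.70 | 25.5% | 11.3% |
| 0.75 | 36.7% | 27.8% |
| 0.80 | 50.3% | 53.5% |
| 0.85 | 65.7% | 80.5% |
| 0.90 | 81.3% | 96.4% |

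The gap changes sign as p rises. It also shrinks at p = 0.85 once women differ in attendance, which selection requires: a beta-binomial model with mean 0.85 gives 66.7% against 72.2% when the between-woman SD is 0.10, and 71.4% against 73.0% when it is 0.20.

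**The case against.** The strongest reply is that this is a supplementary analysis. Intent-to-treat is the main analysis, the sample size is not tied to the per-protocol set, and loss of randomisation is a known weakness of every such set. This stands and limits the seriousness. It does not remove the point: here one arm cannot be filtered at all, and the protocol has already fixed the threshold and the exclusion.

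A second reply is that the size rests on an assumed correlation and that baseline measurement could remove much of the bias. This also stands. The range is illustrative, and selection on untreated change could still remain after adjustment.

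Three stronger readings are tempting, and the document does not support them:
- A reader might infer that the rule deletes every control, since none attends any session. The ordinary reading is that controls have nothing to miss and stay in.
- A reader might infer that the rule systematically favours PAC or StEx. The cut-offs do differ after rounding (87.5% and 81.25%), but step 3 shows no predictable direction. The larger number of contact hours in StEx is by design.
- Because "Once every 15 days, a thematic group class will be offered to participants", a reader might infer that the StEx denominator could be about 40. The article fixes the programme at 32 sessions, and nothing in it describes a 40-session programme.

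A third reply is that an instrumental-variable estimate fits PAC poorly, because its participants' manual, activity tracker and home exercise booklet can act apart from attendance. This is a fair objection to replacing the per-protocol analysis outright. It is weaker against adding the estimate with that limitation stated.

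**Conclusion.** The concern holds for the supplementary control contrasts. As specified, they compare women selected on attendance after randomisation with an unselected control arm, and they can show a difference with no true effect. The selection follows from the design; that it is related to outcome is plausible from the article's own account of barriers and compliance. The size is unknown. It is about 0.04 to 0.32 SD before baseline adjustment if the attendance–outcome correlation is 0.1 to 0.4 and 50 to 80% are kept, and it could be smaller after adjustment. The intent-to-treat results are not touched. For PAC against StEx, only a note on rounding remains. The change should be made, but it is not critical to the trial's main conclusions.

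**What to change.** 1. Keep intent-to-treat as the main analysis.
2. Add a complier-average (instrumental-variable) estimate for PAC against control and for StEx against control. Use randomised arm as the instrument and the logged proportion of sessions attended as the dose received, keep all randomised women, and adjust for the baseline value of the outcome.
3. Label the 80% subset descriptive. State that all controls are retained, and give the cut-offs in whole sessions: 7 of 8 for PAC and 26 of 32 for StEx. Note that these are 87.5% and 81.25% after rounding.

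The cost is analysis wording only, since attendance is already recorded. The new estimate will have wider intervals than intent-to-treat. It also assumes that assignment affects outcome only through attendance. For PAC this is doubtful because of the tracker, manual and home booklet, and it should be stated as a limitation. The added estimate covers the two control contrasts only; PAC against StEx should rest on intent-to-treat.
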